## Delivery and Postpartum Follow-up

1. The midwives will record all birth weights and note any stillbirths and perinatal deaths.
2. Midwives will record all congenital deformities for verification and confirmation by a clinician.
3. Visit all women and babies at 6 to 8 weeks post delivery to obtain reports of any neonatal adverse events such as deaths or morbidity.
4. At 6 weeks post partum, if a woman has peripheral parasitaemia she will be treated with SP and followed up for parasite clearance on days 14 and 28 post treatment. If there is no parasite clearance on day 14 and/or day 28 a course of rescue medication (quinine) will be given. This part of the study is necessary to assess the efficacy of SP to clear parasitaemia.

Figure 1: - Flow chart of proposed study design

**RDT screening and SP case management arm**

Record pregnancy and delivery outcomes (abortions, SB, abnormalities); BW and neonatal jaundice.

Follow-up child at 6 to 8 weeks

Check blood slide of the mother for MP. If positive give a course of SP and follow up on day 14 and day 28

**LLIN plus SP-IPTp and add daily doses of haematinics.**

**LLIN and treatment with SP and daily doses of haematinics for RDT positive cases.**

Randomise pregnant women of 16 – 24 weeks gestation into IPTp and case finding and management arms at ANC sessions.

Passive follow up at 6, 8 & 9 months. Repeat SP-IPTp. Hb at 34 to 36 weeks

**IPTp Arm (not screened)**

**LLIN and daily doses of haematinics only for RDT negative women**

Passive follow up at 6, 8 & 9 months. Repeat RDT screening and treat with SP if she is parasitaemic. Hb at 34 to 36 weeks.

Record pregnancy and delivery outcomes (abortions, SB, abnormalities); BW and neonatal jaundice.

Follow-up child at 6 to 8 weeks

Check blood slide of the mother for MP. If positive give a course of SP and follow up on day 14 and day 28

**RDT screening and AQ+AS case management arm**

**LLIN and treatment with AQ+AS and daily doses of haematinics for RDT positive cases.**

**LLIN and daily doses of haematinics only for RDT negative women**

Passive follow up at 6, 8 & 9 months. Repeat RDT screening and treat with SP if she is parasitaemic. Hb at 34 to 36 weeks.

Record pregnancy and delivery outcomes (abortions, SB, abnormalities); BW and neonatal jaundice.

Follow-up child at 6 to 8 weeks

Check blood slide of the mother for MP. If positive give a course of SP and follow up on day 14 and day 28

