There is currently great international support and momentum to increase the coverage of ITNs use among pregnant women. Thus while looking for alternative drugs for IPT in areas with SP resistance we have to consider the additional benefits of the combination of ITN and IPT over ITN with effective case management approach and the potential drug related adverse outcomes of drugs used for IPTp. The RDT screening and treatment with an effective antimalarial of those with a positive RDT test will reduce the number of women that would be exposed to drugs. Although some women with placental malaria may be missed by the RDT screening, it can be argued that the proportion of women with placental malaria missed by RDT would be minimal if all women used an ITN and that the risk of missed placental malaria will be offset by the reduction in women exposed to antimalarials of uncertain safety profile unnecessarily.

We are proposing this follow up study to determine whether active case finding and management is as effective as intermittent preventative treatment for the control of malaria during pregnancy. A two-armed non-inferiority randomised trial using SP in both arms (LLIN+ IPTp or LLIN + RDT & treatment) is appropriate to address this question. However, if SP is not very effective, a difference may not be found between the two arms since the effect of SP as IPT or treatment would be minimal and the effect of LLIN would be similar in both arms. We cannot replace SP with another effective antimalarial in the IPTp arm since the safety profile of potential antimalarial drugs that could replace SP are not adequately established to be useful for IPTp. A two arm study of LLIN + SP-IPTp and LLIN + RDT & AQ+AS treatment will not be appropriate to prove the principle that LLIN + RDT & treatment is not inferior to LLIN + IPTp since AQ+AS is likely to be more efficacious than SP and this would bias our observation. Thus we propose a three arm trial: (1) LLIN plus SP-IPTp; (2) LLIN plus RDT and treatment with SP (3) LLIN plus RDT and treatment with AQ+AS.

AS+AQ is the first line drug of choice for treatment of uncomplicated malaria in Ghana. However there is very little safety data on the use of AS+AQ for the treatment of malaria during pregnancy and the safety data collected in this study will be very useful for informing the national drug policy for treatment of malaria during pregnancy.

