## Study Design

A three-arm open label randomised control non-inferiority trial of RDT screening with or without treatment with SP or AQ+AS versus IPTp using SP as follows: -

1. OptiMAL® antigen screening and treatment with SP plus LLIN
2. OptiMAL® antigen screening and treatment with AQ+AS plus LLIN
3. SP-IPTp plus LLIN

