## Enrolment Procedures

A schematic profile of the study is shown in Figure 1. All study pregnant women will be recruited from weekly antenatal clinic sessions held at the study sites over a period of one and half years. Three teams of midwives and their assistants put together and trained by the principal investigator (PI) will assist the PI and research teams to conduct the recruitment during antenatal clinic hours. The standard operating procedures at the clinic will be as follows:

1. Randomise pregnant women reporting at the ANC who consent to participate in the study into three arms: an IPTp arm, RDT screening and SP case management arm and RDT screening and AQ+AS case management arm. Distribute LLIN to eligible pregnant women in all arms.
2. Obtain blood for baseline investigations including haemoglobin level, thin and thick blood films for malaria parasite counts and, filter paper blood spots.
3. Assess all pregnant women in the RDT and treatment groups clinically and obstetrically prior to OptiMAL® dipstick screening; for those parasitaemic offer SP or AQ+AS and ingestion of first dose observed directly at the ANC. Encourage the women to regularly sleep under the bed nets provided and take their daily doses of iron and folic acid tablets.
4. For women in the RDT and treatment groups who are negative offer only daily doses of iron and folic acid tablets and encourage them to regularly sleep under the bed nets provided.
5. Women in the IPTp group will receive SP and ingestion directly observed at the ANC according to the national guideline. Encourage the women to regularly sleep under the bed nets provided and take their daily doses of iron and folic acid tablets.
6. Women who decline participation in the study will receive SP-IPTp according to the national guideline.

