## Antenatal Follow-Up Procedures

1. **Day 7:** Women receiving SP or AQ+AS treatment will be followed up actively on the day 7 post treatment to assess any adverse events during the week post treatment.
2. **At 6 months:** repeat SP-IPT for women in the IPT arm and treat women in the case management with SP or AQ+AS if they are RDT positive. Women in the case management arm with negative RDT would receive only haematinics. Ask all study women to regularly sleep under bed nets provided.
3. **At 8 months:** repeat SP-IPT for women in the IPT arm and treat women in the case management with SP or AQ+AS if they are RDT positive. Women in the case management arm with negative RDT would receive only haematinics. Ask all study women to regularly sleep under bed nets provided.
4. **At 34 to 36 weeks:** actively follow up women to sample blood by finger prick for haemoglobin measurements, slide smears for malaria parasite counts and filter paper blood spots.
5. **Unscheduled visits:** Women presenting with a history of fever during an unscheduled visit will be tested for malaria parasite. If they were found parasitaemic, they will be deemed to be treatment failure and will be treated with quinine as rescue medication.
6. All pregnant women would receive haematinics packs at each of the follow ups.

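### Figure 1 tells sites to give SP, not AQ+AS, to women in the AQ+AS arm who test RDT positive at repeat antenatal visits

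*Protocol*

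**What the plan says.** The text defines the third arm consistently:

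- Background & Rationale lists it as "3) LLIN plus RDT and treatment with AQ+AS".
- Study Design lists it as "OptiMAL® antigen screening and treatment with AQ+AS plus LLIN".
- Enrolment Procedures randomises women to an IPTp arm and to an "RDT screening and SP case management arm and RDT screening and AQ+AS case management arm".

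For the visits at 6 and 8 months, Antenatal Follow-Up Procedures (items 2 and 3) tells staff to "treat women in the case management with SP or AQ+AS if they are RDT positive". It does not say which arm gets which drug.

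Figure 1 sets out each arm in boxes. Under the AQ+AS arm's heading, the first box reads "LLIN and treatment with AQ+AS and daily doses of haematinics for RDT positive cases". The antenatal follow-up box of the same arm, for 6, 8 and 9 months, reads "Repeat RDT screening and treat with SP if she is parasitaemic".

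**The concern.** The assigned drug of a randomised arm is stated in two incompatible ways. Under the text, a woman in the AQ+AS arm who tests positive at a repeat visit gets AQ+AS. Under the flow chart she gets SP.

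If sites worked from the flow chart, the two screening arms would differ only in the drug given to women who were positive at enrolment. This matters because of why the third arm exists. Background & Rationale argues that if SP works poorly, a comparison of two SP-based strategies may show no difference simply because SP adds little in either. The AQ+AS arm guards against that, on the expectation that "AQ+AS is likely to be more efficacious than SP". Giving SP at repeat visits would pull this arm towards the SP screening arm and weaken the safeguard.

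The same section wants AQ+AS safety data in pregnancy to inform national drug policy. SP courses within the arm would mix the two exposures.

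**Working it through.** **Comparing the statements.** The protocol gives no figure to reproduce here. The check is which drug each place assigns to an RDT-positive woman in the third arm.

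| Place | Drug |
|---|---|
| Background & Rationale, arm list | AQ+AS |
| Study Design, arm list | AQ+AS |
| Enrolment Procedures, item 1 | AQ+AS |
| Antenatal Follow-Up Procedures, items 2 and 3 | SP or AQ+AS, arm not stated |
| Figure 1, AQ+AS arm heading and first box | AQ+AS |
| Figure 1, AQ+AS arm antenatal follow-up box | SP |

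**Innocent explanations.**

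- *Figure boxes out of order after text extraction.* Figure 1 has three antenatal follow-up boxes. One repeats SP-IPTp and belongs to the IPTp arm. The other two both say to treat with SP. However the boxes are arranged, the AQ+AS arm receives one that names SP, and no follow-up box names AQ+AS.
- *The postpartum course.* Delivery and Postpartum Follow-up says "At 6 weeks post partum, if a woman has peripheral parasitaemia she will be treated with SP". That is a separate step for all women, with its own box in the figure. The disputed box is antenatal.
- *Rescue treatment.* For parasitaemia at unscheduled antenatal visits, rescue is quinine, not SP.
- *A planned switch of drug.* No section describes one.

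None explains the box. The likeliest account is that it was copied from the SP screening arm.

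**Size if the figure were followed.** The protocol gives no RDT positivity by visit, so this is a range under assumptions. Let positivity be *p* at enrolment and *r × p* at each of *k* repeat rounds, with one course per positive screening test. Enrolment courses are AQ+AS and repeat courses are SP, so

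share of courses given as SP = *k r p* / (*p* + *k r p*) = *k r* / (1 + *k r*).

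| *r* (assumed) | *k* = 1 (6 months only) | *k* = 2 (text: 6 and 8 months) | *k* = 3 (figure: 6, 8 and 9 months) |
|---|---|---|---|
| 0.1 | 0.1/1.1 = 9% | 0.2/1.2 = 17% | 0.3/1.3 = 23% |
| 0.25 | 0.25/1.25 = 20% | 0.5/1.5 = 33% | 0.75/1.75 = 43% |
| 0.5 | 0.5/1.5 = 33% | 1/2 = 50% | 1.5/2.5 = 60% |
| 1 | 1/2 = 50% | 2/3 = 67% | 3/4 = 75% |

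If sites follow the text, the share is 0%.

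These are shares of treatment courses, not bias in an endpoint. The primary outcome is Hb at 34 to 36 weeks. Taking a month as about 4.35 weeks, 6, 8 and 9 months are about 26, 35 and 39 weeks. A 9-month course therefore generally comes after that measurement, and an 8-month course falls close to it. The *k* = 1 column is the closest guide for the primary outcome; *k* = 2 and *k* = 3 bear mainly on the safety data.

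**The case against.** The strongest reply is that this is a copied word in a flow chart. The arm is defined as AQ+AS in three sections and in the heading and first box of the same figure, nothing says the figure overrides the text, and a trained team would read the 6- and 8-month instruction by arm. Enrolment Procedures, item 3, uses the same SP-or-AQ+AS shorthand without confusing anyone. On this view the point is a minor correction and rewording the text is a matter of taste.

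Much of that stands. The intended drug is clear, harm requires sites to follow the figure, and the percentages rest on an assumed ratio. The direction of any bias is also the less dangerous one. On the protocol's own expectation that AQ+AS is the better drug, substituting SP would make the arm look worse and non-inferiority to IPTp harder to show, rather than favour a false claim. Treating AQ+AS versus IPTp as one of two primary comparisons is itself a reading: Sample size applies the 5% margin to screening with either drug, while the primary objective speaks of a single screening arm.

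What does not stand is that the text cures the error. Items 2 and 3 never tie drug to arm, Figure 1 is the only place that does so for repeat visits, and Enrolment Procedures opens by sending the reader to that figure. At enrolment the shorthand does no harm because the figure's first box names the right drug. At repeat visits the figure names the wrong one.

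**Conclusion.** The concern holds. The antenatal follow-up box of the AQ+AS arm in Figure 1 is wrong as written and should name AQ+AS. It is an internal inconsistency in the treatment rule of a randomised arm, most likely a copying error, and should be fixed although it does not undermine the design.

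The effect is nil if sites follow the text. If they follow the figure, SP would replace AQ+AS in 17% to 67% of the arm's screening-triggered courses with the two repeat rounds in the text, or 23% to 75% with the three in the figure. Both ranges assume repeat positivity of 0.1 to 1 times that at enrolment, equal across repeat rounds, and one course per positive test. Counting only the 6-month round, which clearly precedes the primary Hb measurement, the range is 9% to 50%. The contradiction itself rests on none of these assumptions.

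**What to change.** 1. In Figure 1, AQ+AS arm, antenatal follow-up box, replace SP with AQ+AS.
2. In Antenatal Follow-Up Procedures, items 2 and 3, tie drug to arm: SP for RDT-positive women in the SP screening arm, AQ+AS for those in the AQ+AS screening arm. The same clarification could be made in Enrolment Procedures, item 3, for consistency.
3. Check that site instructions match.

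Leave the postpartum SP course in the figure as it is, since it is planned for all women. The arm definitions in Background & Rationale and Study Design need no change.

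The cost is a few words and a check of site materials, with no effect on sample size or visits.
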